### Adherence assessment

Adherence to the study regimen will be defined as the extent to which participants comply with study intervention requirements. The SOFTER Pilot study 2 showed that over 95% adherence can be expected in the EMDR group. A log of intervention sessions will be kept for each participant and will include duration, completeness, and patient satisfaction. This log will be regularly reviewed by the Steering Committee and used as part of the decision to continue or discontinue the study.

### Interim analyses and stopping rules

No interim analysis of efficacy is planned. The study can be stopped by the DSMB for safety reasons or because of poor study performance (losses to follow-up > 25%), poor quality control, slow accrual (recruitment rate < 75% than expected), serious adverse events considered to be caused by the intervention, or increased frequency of adverse events. Such findings are presented to the DSMB for review of the events to determine whether there are statistical as well as clinical concerns. The statistician reports their findings to a closed session of the DSMB and these are used to determine what steps will be taken.

### Data analyses

Descriptive and inferential statistical methods will be used to analyze the outcomes and other study data. Confounding variables will include cause of admission (injury versus medical), age group, and sex. The analyses will be conducted as intent-to-treat for primary endpoint and per-protocol for secondary analyses. Randomization codes will only be revealed at the end of the analysis.

Primary analyses will be conducted using a Fisher exact test. A stratified analysis will be carried out considering study center and PCLS risk score. For other variables, Wilcoxon test will assess differences for continuous variables and Fisher exact test for categorical variables.

Differences between patients who completed the study and those who were lost to follow-up will be assessed for all variables.

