### Intervention

Patients in the EMDR group will receive a 1-hour psychotherapeutic intervention, utilizing the R-TEP [40]. This protocol is specially designed for victims of recent traumatic events, and incorporates and extends the early EMDR intervention protocols [32] into an integrative and comprehensive intervention considering the fragmented, unconsolidated nature of recent traumatic memories and the need for safety and containment. Following the eight phases of the standard EMDR protocol, it introduces four new procedural concepts (Traumatic Episode, Episode Narrative, “Google Search/ Scan” for identifying disturbing fragments and Current Trauma Focused processing strategies). These sessions will be carried out by trained psychologists.

Patients in the treatment-as-usual group will be medically and psychologically attended to by ER staff with no intervention of the study psychologist.

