### Protocol deviations

Deviations can affect all aspects of a research protocol such as inclusion, monitoring, measurement of endpoints, and treatment process. All deviations must be documented by the investigator and discussed by the Steering Committee and Data Management Center.

Even in the event of deviation from the protocol, participants must be monitored until the date planned in the protocol.

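### Per-protocol is the only stated analysis of the secondary outcomes, so PTSD and 12-month PCLS have no as-randomised comparison and are open to a probably small selection bias of unknown direction

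*Protocol article*

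**What the plan says.** The Data analyses section sets the analysis populations in one sentence: "The analyses will be conducted as intent-to-treat for primary endpoint and per-protocol for secondary analyses". No intention-to-treat analysis of a secondary outcome appears anywhere else in the article, and the per-protocol set is not defined.

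The secondary outcomes, listed under Methods/design, include 12-month PCLS, 3-month PTSD, recovery expectation, acute and chronic pain, and psychotropic medicine use. The hypothesis at the end of the Background section covers PTSD as well as PCLS.

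Four other statements bear on the point:

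- Intervention: EMDR patients receive a one-hour session. Usual-care patients "will be medically and psychologically attended to by ER staff with no intervention of the study psychologist".
- Adherence assessment, on what is recorded: "A log of intervention sessions will be kept for each participant and will include duration, completeness, and patient satisfaction".
- Adherence assessment, on what is expected: "The SOFTER Pilot study 2 showed that over 95% adherence can be expected in the EMDR group".
- Protocol deviations: deviations may concern inclusion, monitoring, endpoint measurement or treatment. On follow-up, "Even in the event of deviation from the protocol, participants must be monitored until the date planned in the protocol".

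**The concern.** This is a superiority trial. Comparing the arms as randomised protects against selection; a per-protocol comparison gives that up, because patients are removed for something that happened after allocation. Used beside an intention-to-treat analysis, per-protocol does little harm. Here it is the only analysis stated for the secondary outcomes.

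The two arms also differ in how a patient can fail the protocol. An EMDR patient can leave a session unfinished, and the log records this. A usual-care patient has no session to leave. Exclusion on that ground therefore sets a selected EMDR group against a control group not selected in the same way.

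At stake are the PTSD half of the hypothesis and the 12-month PCLS result. Neither would have a stated randomised comparison behind it.

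**Working it through.** **1. The plan's own figure.** The Sample size section gives 169 evaluable patients per group for 47% against 32% (a 15-point decrease), alpha 5% and power 80%. The usual two-sided formula for two proportions gives 166, and power at 169 is 0.808. Inflation: 169 / (0.80 × 0.95) = 222.4, rounded up to the stated 223. Nothing in the point disputes these figures.

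**2. How many patients could be excluded.** Adherence above 95% means at most about 5% non-adherent: 0.05 × 223 = 11.15, about 11 randomised EMDR patients, or 0.05 × 169 = 8.45, about 8 evaluable ones.

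**3. Model.** Suppose there is no treatment effect, so the whole EMDR arm has the control risk *p*. A fraction *a* completes the session, and non-completers have *k* times the completers' risk. Then

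- per-protocol EMDR risk = *p* / (*a* + (1 − *a*) × *k*)
- shift = *p* − that risk (positive values favour EMDR)

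Inputs from the article: *a* = 0.95 (Adherence assessment); *p* = 0.19 for PTSD (pilot control group, Background); *p* = 0.47 for PCLS (Sample size). The 47% is the 3-month planning rate, used here for 12 months by assumption. The article gives no value for *k*, so it is varied. Only exclusion for an incomplete session is modelled.

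| *k* (assumed) | PTSD: per-protocol EMDR risk | Shift (points) | PCLS: per-protocol EMDR risk | Shift (points) |
|---|---|---|---|---|
| 0.5 | 0.19 / 0.975 = 0.1949 | −0.5 | 0.47 / 0.975 = 0.4821 | −1.2 |
| 1 | 0.1900 | 0 | 0.4700 | 0 |
| 1.5 | 0.19 / 1.025 = 0.1854 | +0.5 | 0.47 / 1.025 = 0.4585 | +1.1 |
| 2 | 0.19 / 1.05 = 0.1810 | +0.9 | 0.47 / 1.05 = 0.4476 | +2.2 |
| 3 | 0.19 / 1.10 = 0.1727 | +1.7 | not possible (risk above 1) | – |

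**4. Limits at 5% excluded.**

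- Every excluded patient has the outcome: PTSD (0.19 − 0.05) / 0.95 = 0.1474, shift +4.3 points; PCLS (0.47 − 0.05) / 0.95 = 0.4421, shift +2.8 points.
- No excluded patient has it: PTSD 0.19 / 0.95 = 0.2000, shift −1.0 point; PCLS 0.47 / 0.95 = 0.4947, shift −2.5 points.

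**5. Effect on false-positive risk.** With 169 controls and 169 × 0.95 EMDR patients, take the chance of a nominal 5% two-sided result as Φ(shift/SE − 1.96) + Φ(−shift/SE − 1.96). This is a normal approximation, not the planned Fisher test. It gives about 5.0% to 6.9% over the table. If every excluded patient has the outcome, it gives about 18% for PTSD and 8% for PCLS.

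**6. Under intention to treat.** The shift from exclusion is zero by construction, and 169 and 223 stand. Loss to follow-up is a separate matter that this change does not touch.

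The article gives no rates for pain or recovery expectation, so no shift can be computed for them.

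**The case against.** The strongest reply is that the numbers are small and the mechanism is partly inferred. Most of that stands.

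- **Where exclusions fall.** A reader might infer that the plan removes patients from the EMDR arm only. The article does not say so. The per-protocol set is undefined, and its definition may sit in the full protocol or analysis plan. Errors of eligibility or endpoint measurement can arise in either arm, and a control patient seen by the study psychologist would also deviate. Only exclusion for an incomplete session is one-sided.
- **Direction.** A reader might infer that the bias must favour EMDR because non-completers are sicker or more distressed. The article gives neither their reasons nor their prognosis. Patients who leave early could be milder cases, and the table then changes sign.
- **Size.** A reader might assume 10% or 15% exclusion. At 85% adherence and *k* = 2 the model gives 2.5 points for PTSD and 6.1 for PCLS, but the article expects adherence above 95% and reports no patient refusal in the pilot. Only the 5% case has a basis in the text.
- **Blinding.** A reader might infer that exclusion by session completeness reveals the EMDR arm to the blinded analyst. This is speculative: data management could flag the set without naming the arm, and a supportive per-protocol analysis would raise the same issue.
- **Scope of the claim.** The article's title names only post-concussion-like symptoms; PTSD enters through the hypothesis.
- **Wording.** *Secondary analyses* could mean supportive analyses of the primary endpoint, which is close to the fix below. That is the less natural reading, since the sentence confines intention to treat to the primary endpoint. Even then it leaves the population for the secondary outcomes unstated in the article and needs rewording.

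None of this supplies a reason to make per-protocol the sole analysis of outcomes for which as-randomised data will be collected.

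**Conclusion.** The concern holds in a limited form. On the natural reading, the article states no as-randomised comparison for any secondary outcome, and one ground for exclusion exists only in the EMDR arm. That creates a risk of selection bias, not a demonstrated bias, and its sign is unknown.

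The probable size is about 0.5 to 2 points in favour of EMDR. This rests on 5% exclusion for incomplete sessions, no true effect, the pilot PTSD rate of 19% or the planning PCLS rate of 47%, and an assumed higher risk in non-completers. Equal risks give zero and lower risks reverse the sign. The ceilings of 4.3 points (PTSD) and 2.8 points (PCLS) require every excluded patient to have the outcome.

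The primary endpoint is analysed by intention to treat and is unaffected. The point should be fixed, but it does not threaten the trial's main conclusion.

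**What to change.** Replace the sentence in Data analyses with wording such as: *The primary and all secondary endpoints will be analysed by intention to treat, including all randomised patients with outcome data in their allocated arm. A per-protocol analysis will be reported as supportive only.* State which deviations remove a patient from the per-protocol set, in either arm, before the randomisation codes are revealed.

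The cost is one sentence and one definition. No extra data are needed, since patients with deviations are already followed to the planned date, and the sample size does not change. The secondary estimates will be slightly diluted. For example, if non-completers gain nothing, a 15-point effect in completers averages 0.95 × 15 = 14.25 points at 95% adherence.

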**Fig. 2 Fig2:**
[figure not shown]
Schedule of enrolment, interventions, and assessments

A set of three items will be recorded for each injured patient, including sex (+ 1 for female), perceived health status prior to admission (excellent, very good: 0; good: + 1 poor: + 2; bad: + 3), current use of anxiolytics/antidepressants (+ 1 if yes).

To be enrolled in the study, the patient will need to score above a pre-defined threshold of 2 on the scoring procedure based on the three items and designed to select patients at risk for PCLS. The score has been developed using data from the Pericles study and validated on data of the SOFTER Pilot 1 and 2 studies.

Patients fulfilling inclusion criteria and assessed as at risk for PCLS will be presented with the objective and procedures and invited to sign an informed consent form. A screening log will be filled in to describe reasons for ineligibility and for non-participation of eligible candidates.

The randomization procedure for assigning a participant to an intervention group will then be performed and the results will be recorded in the Shared Study Monitoring System. Electronic block randomization will be stratified according to study center. Block sizes will be randomly modified and kept secret.

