### Sample size

The study sample size is calculated using PCLS rates expected at 3 months after an ER admission in a patient population assessed to be at high risk of PCLS.

Our pilot study showed that, using the criteria described above, the incidence of PCLS among patients selected and enrolled in the study will be of approximately 47%. Our aim is to design the present study to be able to evidence a 15% decrease in PCLS prevalence in the EMDR group. Assuming an alpha risk of 5% and a power of 80%, the required sample size will be 169 patients in each group. We further assumed 20% loss to follow-up and 5% missing data for the main variables. Thus, we plan to include 223 patients in each group (112 per center in each group).

A study therapist will be available from 10 am to 6 pm, 5 days a week. Considering EMDR session duration and emergency care, patients will be assessed for eligibility from 8 am to 6 pm. Data from our ER registry and experience from our pilot study show that, during this period, approximately 50 patients will be assessed for eligibility. The screening tool used in this study will select approximately 10% of patients admitted to the ER. We also estimate that 10% of eligible patients will be missed in the ER and assume a 5% refusal rate. Consequently, we can expect approximately four inclusions per day, corresponding to an inclusion period of 3 months.

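### The primary analysis is a pooled Fisher exact test with about 78% power at the planned size, while the stratified analysis already planned on center and risk score is left in a supporting role

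*Protocol article*

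**What the plan says.** The Data analyses section fixes the test: "Primary analyses will be conducted using a Fisher exact test. A stratified analysis will be carried out considering study center and PCLS risk score". The article gives no other rank for the stratified analysis, so on its plain wording Fisher is primary. The same section adds: "Confounding variables will include cause of admission (injury versus medical), age group, and sex".

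Under Study enrollment procedures and randomization: "Electronic block randomization will be stratified according to study center". Randomization is not stratified by the risk score. The score is an entry criterion, however, so it is known for every randomized patient. It is built from sex, prior perceived health and current psychotropic medication.

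The Sample size section puts PCLS in the enrolled population at about 47%, aims to "evidence a 15% decrease in PCLS prevalence in the EMDR group", and states: "Assuming an alpha risk of 5% and a power of 80%, the required sample size will be 169 patients in each group". It continues: "We further assumed 20% loss to follow-up and 5% missing data for the main variables". This leads to 223 per group.

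**The concern.** The sample size promises 80% power, but the test named as primary may not deliver it. Fisher's exact test holds its size below the nominal 5% and loses power compared with the large-sample tests on which sample-size formulas usually rest. The trial also records a score designed to pick out patients at risk of the primary outcome, and already intends to stratify on it, yet the headline p-value comes from the pooled table. At stake are a few points of power in a confirmatory trial, and a stated power that does not belong to the stated test.

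**Working it through.** **Inputs from the article.** Control rate 0.47; intervention rate 0.47 − 0.15 = 0.32; alpha 5%; power 80%; 169 evaluable per group; 20% loss and 5% missing data; 223 enrolled per group. The article does not say whether alpha is two-sided or whether 15% is absolute. Two-sided and absolute are the readings that come near 169. A relative 15% (0.47 to 0.40) would need 775 per group, and a one-sided test 131.

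**Step 1: the plan's own figure.** Large-sample formula with pooled null variance, where p̄ = 0.395:

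n = [1.960·√(2·0.395·0.605) + 0.842·√(0.47·0.53 + 0.32·0.68)]² / 0.15² = (1.355 + 0.575)² / 0.0225 ≈ 166.

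Variants: unpooled 163, arcsine 166, continuity-corrected 179. The stated 169 lies within three patients of 166. Attrition: 169 / 0.80 / 0.95 = 222.4, so 223. Both figures are accounted for.

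**Step 2: the test actually named.** Sum Bin(x₁; 169, 0.47)·Bin(x₂; 169, 0.32) over all tables whose two-sided Fisher p-value is at most 0.05. Do the same for chi-square without correction. For the true size, set both rates to 0.395.

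| Test, 169 per group | Power | True size |
|---|---|---|
| Fisher exact | 78.0% | 3.95% |
| Chi-square | 81.2% | 5.15% |

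Fisher gives 79.9% at 179 per group and 80.2% at 180. With the plan's attrition, 180 / 0.80 / 0.95 = 236.8, or 237 enrolled per group instead of 223. This step uses only the article's inputs.

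**Step 3: what stratification adds.** The article gives no PCLS risk by score, so this step rests on assumptions: three score classes with shares 50/35/15%, an odds ratio of 1 to 3 per score point, a center odds ratio of 1 or 1.5, a common treatment odds ratio set so that the marginal rates stay at 47% and 32%, and 84 and 85 patients per arm in the two centers. The CMH statistic is |Σ(a − n₁m/T)| / √Σ[n₁n₂m(T − m) / (T²(T − 1))] over strata, rejecting at 1.96. Here a is the number of events in one arm, m the events in both arms, n₁ and n₂ the arm sizes, and T = n₁ + n₂. With 40,000 trials per row, the Monte Carlo standard error is about √(0.8·0.2/40,000) = 0.2 point.

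| OR per score point | Center OR | Fisher | Chi-square | CMH, center | CMH, center × score |
|---|---|---|---|---|---|
| 1.0 | 1.0 | 78.0% | 81.2% | 81.2% | 80.4% |
| 1.5 | 1.5 | 77.6% | 81.0% | 81.0% | 81.1% |
| 2.0 | 1.0 | 78.4% | 81.5% | 81.5% | 82.8% |
| 3.0 | 1.0 | 77.9% | 81.1% | 81.1% | 85.4% |
| 3.0 | 1.5 | 78.0% | 81.3% | 81.3% | 85.7% |

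Center alone adds at most 0.1 point over chi-square. Center × score ranges from 0.8 point below chi-square (score not prognostic) to 4.5 points above. Its type I error was 4.8% to 5.3% over all scenarios run.

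**Step 4: is the stratifier ready?** Inclusion criteria asks for a score above 1 and counts anxiolytics. Study enrollment procedures and randomization asks for a score above 2 and counts anxiolytics or antidepressants. The items sum to at most 1 + 1 + 3 = 5. The first threshold leaves four score values (2 to 5) and the second leaves three (3 to 5), so the number of strata over two centers is 8 or 6 depending on which text holds.

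**The case against.** The best defense is that nothing here is invalid. Fisher controls type I error, and ignoring the center strata makes it conservative if anything. The stratified analysis is planned on exactly the two useful variables. Its method, and the way cause of admission, age group and sex enter, are details that an article may leave to the full protocol or SAP. All of this stands, and none of it is counted against the plan. What remains is that the article does state which test is primary, and that test does not have the stated power at the stated size.

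Several stronger readings are tempting but unsupported:

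- **That the power is lost by ignoring center.** The loss shown from the article's inputs comes from the conservatism of the exact test; stratifying by center recovers almost none of it.
- **That stratification by itself is worth 2 to 8 points.** The gap between Fisher and the center × score CMH test (2.4 to 7.7 points in these simulations) combines two changes: leaving the exact test, worth about 3 points, and using the score, worth −0.8 to +4.5. The top of the range assumes a strongly prognostic score. Every enrolled patient has already passed the score threshold, which narrows its range and may weaken it.
- **That the two analyses have no order.** The wording makes Fisher primary.
- **That psychotropic use at 3 months is wrongly analyzed.** The article does not say whether that outcome is any use or an amount, and adjusting for baseline use would be a minor gain on a secondary outcome.

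**Conclusion.** The point holds as a matter of efficiency and of consistency between test and sample size. On the article's inputs, read as two-sided 5% and a 15-point absolute difference, the primary test has 78.0% power with 169 evaluable per group. That is about 2 points below the stated 80% and about 3 below chi-square. If more patients are evaluable than planned, the shortfall goes: with all 223 per group Fisher has about 88%.

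Making the stratified analysis primary restores about 80% power even if the score predicts nothing, and gives up to about 85% if it predicts strongly. Only the first of these should be relied on. The price is up to about 1 point against a plain chi-square test if the score is not prognostic. This is a worthwhile improvement at almost no cost, not a flaw that threatens the validity of the trial.

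**What to change.** Before unblinding, name the stratified analysis as primary: a CMH test stratified by center and risk score, with the common risk difference and its 95% CI. Keep the pooled Fisher test as a sensitivity analysis. Because the arm codes are to be revealed only at the end of the analysis, the change should be dated before any comparison by coded arm.

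First reconcile the two statements of the score threshold and of its medication item, then fix the score classes that serve as strata. Do not add sex as a separate stratum, because it is already a score item.

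If Fisher stays primary, restate its power as about 78% at 169 evaluable per group.

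The cost is a few sentences in the protocol or SAP. No new patients or data are needed, since center and score are already recorded for everyone.

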Following the Pericles project, we conducted a pilot study to identify the factors explaining the persistence of symptoms 3 months after an injury event. The key result of this pilot study (manuscript submitted) was that the stress level reported by patients at the end of their ER stay was a powerful predictor of PCLS and PTSD, irrespective of the stress level reported on entering the ER. This important result prompted us to consider testing the feasibility and then the effectiveness of stress management interventions during an ER stay, in the hope of improving the outcomes of traumatized patients.

Results from the literature and these two studies led us to initiate a literature search for the best intervention candidates that would have the potential to lower stress levels during an ER stay.

One of the first ideas proposed for patients who experience a stressful event was to initiate a stress management procedure before the consolidation of stressful memories. This is partly why the practice of psychological debriefing, which consists of debriefing sessions conducted 2–10 days after the critical incident, has been widely disseminated. However, several critical reviews [18] and a Cochrane review [19] have concluded that this form of intervention leads to an increased rate of PTSD.

More promisingly, early exposure therapy, which is based on the extinction of fear through engagement with traumatic memories and clues, appears to be an effective treatment of PTSD [20, 21]. PTSD syndrome can be interpreted as a failure of recovery caused, in part, by failure of the extinction of trauma [22]. This is supported by research conducted on animals showing that early extinction has the potential to alter the consolidation of memory of original fear [23–25]. Rothbaum et al. [18] were the first to show the effectiveness of an extinction-type intervention (prolonged exposure) beginning in the ER in the prevention of PTSD in a sample of 137 patients randomized to three groups. The intervention also included two other sessions 1 and 2 weeks later. The same authors showed that such short-term intervention could also lower PTSD risk in patients with genes previously found to be associated with stress response [26]. Trauma-focused cognitive behavioral therapy delivered within weeks of a potentially traumatic event for people showing signs of distress was also effective in the treatment of acute stress and early PTSD symptoms, and in the prevention of PTSD [27–31].

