The ERP is a short procedure implemented according to procedures designed and tested in emergency contexts, including the ER [40, 41]. The individuals who arrive at the ER show a wide range of disturbance. The greatest benefit of the ERP intervention is expected for patients in a ‘highly agitated’ state (scoring 7–10/10 on the Subjective Units of Disturbance scale, where 0 = no disturbance and 10 = the highest disturbance possible) to those who have moved into a ‘silent terror’ (scoring 10+/10 on the Subjective Units of Disturbance scale).

The R-TEP is an early EMDR current trauma-focused intervention that incorporates and extends the main ideas of the original Recent Event Protocol guidelines first described by Shapiro and Laub in 2008 [42].

The ICD-10 established a set of diagnostic criteria for PCS. In order to meet these criteria, a patient must have had a head injury *“usually sufficiently severe to result in loss of consciousness*” followed by the development, within 4 weeks, of at least three of the eight following symptoms: headache, dizziness, fatigue, irritability, sleep problems, concentration problems, memory problems, and problems tolerating stress. There is relatively little systematic research on the prevention and treatment of PCS [43–46]. A systematic review published in 2010 [45] suggested that cognitive behavioral therapy may be effective in the treatment of PCS. However, the authors found no quality studies and call for more rigorous trials of cognitive behavioral therapy for post-concussion symptoms. Other strategies include information, education and reassurance [47–49]. An emerging literature points to the independent impact of expectations and coping on chronic conditions following trauma, in particular for patients with whiplash and low back pain [50–55]. Reassurance, as provided in the context of cancer [50], low back pain [51, 52], and mild head trauma [47, 49], was found to help patients in their recovery process. It is therefore possible that at least a subgroup of patients who experienced a traumatic injury may benefit from such intervention.

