## Methods/design

The main objective in our two-site, open-label, randomized controlled trial is to compare the impact on 3-month PCLS of early EMDR R-TEP intervention and usual care in patients presenting to the ER. Secondary objectives include the comparison between EMDR R-TEP and control of 3-month PTSD, 12-month PCLS, self-reported stress at ER discharge, self-assessed recovery expectation at discharge and 3 months, and self-reported pain at discharge and 3 months.

The outcomes are therefore defined as follows:

Primary outcome3-month PCLS as measured with the Rivermead Post-Concussion Symptoms Questionnaire [54]Secondary outcomes12-month PCLS as measured with the Rivermead Post-Concussion Symptoms Questionnaire3-month PTSD as measured with PTSD Checklist-5 [55]Self-assessed recovery expectation at discharge and 3 monthsSelf-reported chronic pain at 3 monthsSelf-reported acute pain at dischargePsychotropic medicine use at 3 months as measured by drug delivery data extracted from the Caisse national d’assurance maladie des travailleurs salariés (CNAM-TS) database, the French social insurance system

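### The only method named for continuous secondary outcomes is an unadjusted Wilcoxon test; for stress (and pain) at ER discharge this is valid, but gives up precision if arrival ratings exist and correlate with discharge ratings

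*Protocol article*

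**What the plan says.** All references are to the protocol article; no statistical analysis plan is shown.

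- **Test.** Data analyses gives one general rule for variables other than the primary outcome: "Wilcoxon test will assess differences for continuous variables and Fisher exact test for categorical variables".
- **Covariates.** The same section states: "Confounding variables will include cause of admission (injury versus medical), age group, and sex". It does not say which outcomes or which model this list serves.
- **Stratification.** It adds: "A stratified analysis will be carried out considering study center and PCLS risk score". This follows directly on the primary Fisher test. Neither list contains stress or pain on arrival.
- **Outcomes concerned.** The secondary objectives in Methods/design include "self-reported stress at ER discharge, self-assessed recovery expectation at discharge and 3 months, and self-reported pain at discharge and 3 months". No scale is given, and the outcome list that follows names acute pain at discharge but not discharge stress.
- **Role of stress.** Background reports from an earlier pilot that "the stress level reported by patients at the end of their ER stay was a powerful predictor of PCLS and PTSD", and that this held "irrespective of the stress level reported on entering the ER". That pilot therefore recorded stress on entry. The text does not say whether this trial does.

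**The concern.** Patients reach the ER with differing levels of stress and pain. Background says as much: "The individuals who arrive at the ER show a wide range of disturbance". If a patient's level at discharge depends partly on the level at arrival, a test on discharge values leaves that variation in the error term. An analysis adjusted for a rating taken before randomisation removes it.

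This matters most for stress. The rationale is that lowering stress during the ER stay prevents later symptoms, so "self-reported stress at ER discharge" is the outcome closest to the supposed mechanism. The pilot's predictive finding took entry stress into account, whereas the comparison planned here names no such term. A noisy comparison could miss a real, moderate reduction in stress and leave the 3-month result without its explanation. Pain at discharge raises the same question of precision, but the article does not present pain as the mechanism.

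**Working it through.** **1. The plan's own figure.** The article gives no power, SD or effect for discharge stress or pain; its only calculation is for 3-month PCLS. With 47% against 32%, two-sided alpha of 5% and power of 80%, the pooled formula is

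n = [1.96 × √(2 × 0.395 × 0.605) + 0.8416 × √(0.47 × 0.53 + 0.32 × 0.68)]² / 0.15² = 165.6, so 166 per arm,

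against 169 stated (within 3%). For enrolment, 169 / (0.80 × 0.95) = 222.4, so 223, as stated. Neither figure is in dispute. I use 223 per arm below because discharge ratings precede the 3-month losses. The per-protocol set for secondary analyses would be slightly smaller.

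**2. Assumptions not in the documents.** Shift d = 0.25 SD (0.20 and 0.40 as alternatives); arrival-discharge correlation r = 0.3, 0.5 or 0.7; approximately normal ratings; two-sided 5%.

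**3. Formulas.**
- Adjusted analysis: SE = √[(2/223) × (1 − r²)] in SD units.
- Wilcoxon: efficiency 3/π relative to the t-test under normality, so an effective n of 223 × 3/π = 212.9 and SE = √(2/212.9) = 0.0969.
- Power = Φ(d/SE − 1.96).

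**4. Results at d = 0.25.**

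| Analysis | SE | d/SE | Power | Variance removed | Equivalent n per arm |
|---|---|---|---|---|---|
| Wilcoxon, unadjusted | 0.0969 | 2.58 | 73% | – | – |
| Linear, unadjusted | 0.0947 | 2.64 | 75% | 0 | 223 |
| Adjusted, r = 0.3 | 0.0903 | 2.77 | 79% | 9% | 245 |
| Adjusted, r = 0.5 | 0.0820 | 3.05 | 86% | 25% | 297 |
| Adjusted, r = 0.7 | 0.0676 | 3.70 | 96% | 49% | 437 |

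The equivalent n is 223 / (1 − r²), relative to the unadjusted linear analysis. About two points of the gain over Wilcoxon come from moving to a linear model under normality. Keeping the 3/π factor for a rank-based adjusted analysis gives 77%, 85% and 95%, so most of the gain at r = 0.5 and 0.7 comes from the adjustment itself.

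**5. Sensitivity to the shift.**
- At 0.20 SD: Wilcoxon 54%; adjusted 60%, 68% and 84% at r = 0.3, 0.5 and 0.7.
- At 0.40 SD: Wilcoxon already 98%; adjusted 99% or more. Little remains to be gained.

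**6. Check on a coarse scale.** Ratings were simulated on a rounded 0–10 scale, with 2,000 runs per setting (Monte Carlo error about 1 point near 73%). At 0.25 SD, Wilcoxon rejected in 72–73% of runs and ANCOVA in 77%, 85% and 95% at r = 0.3, 0.5 and 0.7. With no effect, both rejected in 4–5%. The gain is not an artefact of exact normality, and both methods hold their level.

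**The case against.** Several points against the concern have force.

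- **The text does not say that discharge values are compared alone.** A reader might infer that from the Wilcoxon rule, but the rule is one generic sentence. The confounder list, which neither a Wilcoxon nor a Fisher test can use, implies some adjusted analysis that the article does not describe. This stands. What remains is that the only method named takes no covariate and that no arrival rating is listed anywhere in the section.
- **A reader might infer that arrival ratings are collected and then ignored.** The text does not support this. Entry stress is documented for an earlier pilot only, and the schedule for this trial is in a figure that is not shown. The scales are not stated either; if the ratings are categorical, the Wilcoxon rule does not apply to them.
- **A reader might infer bias or an invalid test.** Neither follows. Under randomisation the unadjusted test keeps its type I error, and its sampling error already covers chance imbalance. The per-protocol set for secondary analyses is a separate matter; with more than 95% adherence expected in the EMDR group (Adherence assessment), its effect here should be small.
- **The supporting text is thin on size.** The remark about a wide range of disturbance comes from the description of a different procedure (the ERP) and concerns ER arrivals in general. No arrival-discharge correlation is reported. At r = 0.3 the gain is modest, and at 0.40 SD it is negligible.
- **Covariates for a secondary outcome are ordinary analysis-plan detail.** This is true where a document is silent. Here a specific method is named, and a more efficient one is available at little cost, so a comment on the choice is fair.

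**Conclusion.** The point holds as one of efficiency. Data analyses names an unadjusted Wilcoxon test as the only method for continuous secondary outcomes and lists no arrival rating as covariate or stratum. If arrival ratings of stress and pain are recorded and correlate with discharge ratings, this gives up precision. At an assumed shift of 0.25 SD with 223 per arm, power is about 73%, against about 79% (r = 0.3), 86% (r = 0.5) or 96% (r = 0.7) after adjustment. Both the shift and the correlation are assumptions.

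The argument from mechanism applies to discharge stress only; for acute pain there is only the gain in precision. The primary analysis, the sample size and the type I error of the secondary tests are unaffected.

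**What to change.** In Data analyses, state that discharge stress, and likewise discharge pain, will be compared with adjustment for center (the randomisation stratum) and, where it is recorded, for the pre-randomisation rating on the same scale. Use ANCOVA, or an ordinal or rank-based model if the scale is coarse, and keep Wilcoxon as a supporting analysis. Where ratings exist, this is a change of wording only, to be fixed before the randomisation codes are revealed.

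If no arrival rating is scheduled, one short self-rating per outcome before randomisation could be added only while recruitment is open. Trial status expected recruitment to finish by June 15, 2018, before the article's publication on 2018-10-12, so that option may have passed. In that case adjust for center and the baseline variables already listed, whose gain would depend on how well they predict the discharge ratings.
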